# Effects and central mechanisms of acupuncture for post-stroke vascular vertigo: study protocol of a multicenter, randomized, sham-controlled trial

**DOI:** 10.3389/fneur.2026.1729679

**Published:** 2026-03-25

**Keywords:** acupuncture, central mechanisms, randomized controlled trial, stroke, vascular vertigo

## Abstract

**Background:**

Vascular vertigo is a common sequela following stroke, significantly impairing patients’ quality of life and rehabilitation progress. Although Western pharmaceutical treatments are widely used, their long-term efficacy is limited and associated with side effects. Acupuncture, a traditional Chinese medical therapy, has potential advantages in alleviating vertigo symptoms. This study aims to evaluate the efficacy and central mechanisms of acupuncture for post-stroke vascular vertigo (PSVV).

**Methods:**

This study is a multicenter, double-blind, randomized controlled trial planned to enroll 234 patients with PSVV from four subcenters. Participants will be randomly assigned in a 1:1:1 ratio to the acupuncture group, the sham acupuncture group, or the active drug group. The trial comprises a 1-week induction period, a 3-week treatment period, and follow-up periods at 8 weeks and 20 weeks. Following the induction period, the drug group will receive betahistine mesilate tablets orally, the acupuncture group will receive needling at Baihui (GV20), Fengchi (GB20), Wangu (GB12), and Taichong (LR3), and the sham acupuncture group will receive superficial needling at non-acupoints combined with blunt needle. All groups will undergo intervention 3 weeks. The primary outcome will be the Dizziness Handicap Inventory (DHI), with secondary outcomes including the Dizziness and Anxiety Rating Scale (DARS), dizziness diaries, the 36-Item Short Form Health Survey (SF-36), transcranial Doppler ultrasonography (TCD), multimodal magnetic resonance imaging (MRI), and Expectation Rating Scale (ERS). The relationship between clinical efficacy and the mechanisms of the prescribed interventions will be explored. Treatment safety will be assessed through adverse event records.

**Discussion:**

This trial will be the first to compare the efficacy of acupuncture, sham acupuncture, and Western medication in treating PSVV. It aims to demonstrate whether acupuncture is safe and effective for this condition and to elucidate its central nervous system mechanisms. We anticipate that this research will provide clinical evidence for the management of PSVV.

**Ethics and dissemination:**

The Medical Ethics Committee of the Chengdu University of Traditional Chinese Medicine Affiliated Hospital has given study approval (approval no. 2025KL-062). The findings will be disseminated through publications, conferences, and briefs to professional organizations.

**Clinical trial registration:**

http://itmctr.ccebtcm.org.cn, identifier ITMCTR2025001283.

## Introduction

1

Recently, diagnostic criteria for Vascular Vertigo were presented by the Bárány Society’s Committee for the Classification of Vestibular Disorders. Vascular vertigo refers to vertigo caused by vascular lesions, typically presenting as acute vestibular syndrome (AVS), characterized by the acute onset of vertigo with nausea or vomiting, head-motion intolerance, and unsteadiness (1). The classification includes vertigo due to stroke or transient ischemic attack as well as vertebral artery compression syndrome, and isolated labyrinthine infarction/hemorrhage, with stroke being the common cause of vascular vertigo (2). Vertigo is also an independent risk factor for stroke patients (3, 4). Post-stroke vascular vertigo (PSVV) is primarily caused by cerebral ischemia or hemorrhage, encompassing both anterior circulation and posterior circulation strokes (5, 6). Post-stroke recovery of cognition, aphasia, upper limb, mobility, and fatigue has received particular attention, yet the accompanying symptom of vertigo is often overlooked (7, 8). Furthermore, recurrent episodes of vertigo increase the risk of stroke recurrence and mortality (9).

The rehabilitative effect of acupuncture, the most widely used complementary alternative medicine method for stroke, has gained international recognition (10). In recent years, acupuncture treatment for vascular vertigo has gained increasing attention among clinicians. Clinical studies indicate that acupuncture is safe and effective for patients experiencing vertigo following a stroke (11). However, the advantages and the underlying mechanisms of acupuncture and moxibustion in the treatment of PSVV have not yet been fully elucidated.

Multimodal magnetic resonance imaging (MRI) is widely used in clinical practice and research of neurological and psychiatric disorders, as it visually reflects brain function and structural changes—making it a key technique in stroke research (12). Specifically, resting-state functional MRI (rs-fMRI), a connectomics tool, focuses on short-term brain network connectivity changes (13) and aids in vertigo prognosis assessment (14). Research has found that vertigo involves multiple vestibular and non-specific networks, and is associated with the cortico-basal ganglia-cerebellum-thalamus network (15). Meanwhile, white matter plays a crucial role in vertigo and imbalance caused by vestibular dysfunction (16). Diffusion tensor imaging (DTI) quantifies the integrity, directionality, and connectivity of white matter fiber tracts by detecting the diffusion characteristics of water molecules within brain tissue (17). Additionally, DTI can investigate differences in connectivity within the vestibular projection pathways (18). Therefore, exploring the neuroplasticity underlying acupuncture treatment for vascular vertigo using these two neuroimaging techniques holds both fundamental and clinical significance.

Therefore, this multicenter randomized controlled trial will evaluate the efficacy of acupuncture in treating PSVV and explore the central mechanisms underlying acupuncture’s therapeutic effects in alleviating vertigo symptoms among stroke patients.

## Study design and methods

2

### Objectives

2.1

This study has two primary objectives: (1) compare the clinical efficacy of real acupuncture, sham acupuncture, and active drugs for PSVV to verify acupuncture’s efficacy and safety for this condition; (2) explore the central nervous system mechanisms of acupuncture for PSVV using multimodal MRI.

### Design and setting

2.2

This is a multicenter, double-blind, randomized, controlled study that meets the recommendations of the Standard Protocol Project: Intervention Trials guidelines (19). This trial will be conducted in four clinical subcenters: the Affiliated Hospital of Chengdu University of Traditional Chinese Medicine, Chongqing Hospital of Traditional Chinese Medicine, Shuangliu District Hospital of Traditional Chinese Medicine in Chengdu, and Longquanyi District Hospital of Traditional Chinese Medicine in Chengdu. A total of 234 eligible participants will be randomly assigned to the active drug group, the acupuncture group, and the sham acupuncture group (1:1:1 allocation ratio). Participants will be evaluated at baseline, week 3, week 11, and week 23. Transcranial Doppler ultrasonography (TCD) and multimodal MRI will be performed at baseline and at week 3. All outcome assessors will be blinded to group assignment. The flowchart and results evaluation schedule of this trial are shown in Figure 1 and Table 1. The protocol was approved by the Medical Ethics Committee of the Affiliated Hospital of Chengdu University of Traditional Chinese Medicine (approval no. 2025KL-062) (Supplementary File 1) and is registered with the International Traditional Medicine Clinical Trial Registration Platform (registration no. ITMCTR2025001283).

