### Randomization and blinding

2.6

All eligible participants will be randomly assigned to three groups at a 1:1:1 ratio using computer-generated random numbers sealed in opaque envelopes. Dedicated personnel responsible for randomization will open the envelopes in enrollment order and inform treating physicians of group assignments. All steps in the implementation of this trial’s randomization protocol will be conducted by dedicated randomization staff who are not involved in the trial itself. Blinding of the acupuncture practitioners will not be feasible due to the nature of the interventions. Nevertheless, the principle of blinding will be consistently upheld throughout the trial: participants in the acupuncture group and sham acupuncture group will receive treatment in separate, partitioned rooms to prevent interaction with other groups. After the 3-week treatment period, a blinding assessment will be conducted for these two groups to evaluate the perceived treatment type (real acupuncture, sham acupuncture, or undetermined) based on participants’ experience. Throughout the trial, the principle of separating researchers, operators, and statisticians will be strictly followed.

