### Interventions

2.7

All participants will receive basic treatment prior to intervention. Per the *Chinese Guidelines for Secondary Prevention of Ischemic Stroke and Transient Ischemic Attack* (21), this basic treatment includes three aspects: (1) Controlling risk factors such as blood pressure and blood glucose; (2) Administering regular-dose aspirin for antiplatelet aggregation (if no contraindications) and atorvastatin for lipid regulation and plaque stabilization; (3) Providing health education on diet, lifestyle, and physical activity. Participants in the acupuncture and sham acupuncture groups will receive a 3-week intervention: one 30-min session daily, 5 times weekly (2 rest days on weekends). The active drug group will take betahistine mesilate tablets orally three times daily for three consecutive weeks.

In the acupuncture group (Group A), participants will undergo acupuncture with filiform needles (Huatuo brand, Suzhou, China; Figure 2) at the following acupoints: Baihui (GV20), bilateral Fengchi (GB20), bilateral Wangu (GB12), and bilateral Taichong (LR3) (Figure 3; Table 2). After needling the acupoints, needles will be twisted 90–180° and lifted and inserted by 3–5 mm to induce a *deqi* sensation. This stimulation will be applied immediately after insertion and then repeated at 10-min intervals during the 30-min needle retention period, yielding three stimulation episodes per treatment session.

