## Discussion

3

The Bárány Society published diagnostic criteria for vascular vertigo in 2022 after a decade of research (2). It should be emphasized that, although the Bárány Society’s definition of vascular vertigo includes both central and peripheral vascular lesions, the present trial is restricted to PSVV. As a result, the findings of this study will be directly applicable to patients with brainstem, cerebellar, or other central vestibular stroke sequelae, but not to isolated labyrinthine infarction or other purely peripheral vascular vestibular syndromes, which require separate investigation. Based on these criteria, this study designs a multicenter, randomized, double-blind trial to evaluate acupuncture’s efficacy for PSVV and explore neuroplasticity mechanisms. This trial is the first to examine a standardized acupuncture protocol for PSVV and conduct neuroimaging research. Combining DTI and rs-fMRI results will enable evaluation of white matter microstructure and gray matter function improvements after acupuncture.

Notably, sensations such as dizziness, vertigo, and unsteadiness can be subjective and poorly defined in stroke patients’ self-reports, so clinicians must discern them more clearly (26). Vertigo is a motion illusion from spatial disorientation, with patients perceiving themselves/surroundings as spinning, tumbling, or tilting. Dizziness is described as head heaviness, lightheadedness, or floating. Unsteadiness presents as unstable gait, imbalance, or a feeling of impending fall—typically absent when lying/sitting. A study reported a significantly increased prevalence of balance problems and associated psychiatric symptom burden (27). PSVV primarily arises from central vestibular pathway damage after stroke (28). Some patients may develop Post-stroke pusher syndrome, primarily due to impairments in proprioception, cerebellar coordination, and damage to pyramidal or extrapyramidal systems. It is characterized by active tilting toward the hemiplegic side and resistance to correction (29). These conditions are distinct from true PSVV and require careful differentiation.

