To ensure reliable results, participants will be randomly assigned to groups, with outcome assessors and statisticians blinded to group assignments to minimize potential bias. However, this trial has several limitations. Owing to the inability to blind among the acupuncturists, the use of self-reported outcomes, and the potential placebo effect of acupuncture, the study results may be prone to bias. Additionally, a challenge for clinical applications of rs-fMRI is the potentially confounding effect of concomitant vascular diseases, aging, or medication on the neurovascular coupling and consequently the fMRI imaging response (33). Therefore, quality control methods are prerequisites for reliable results: (1) recruit right-handed patients for MRI to avoid dominant hand effects on brain structure and function; (2) acupuncture procedures will be strictly performed by trained, certified practitioners with at least 3 years of experience following standardized protocols; (3) Standardized, highly repeatable acupuncture interventions; (4) participants will be instructed to maintain their usual lifestyle for 24 h before scanning, avoiding late nights, smoking, and consumption of coffee or tea. During scanning, participants will close their eyes and wear earplugs. Following the scan, participants will document sensations experienced during the procedure, including somatic sensations, psychological state, and thought activity, to explore the influence of various factors on test outcomes.

In summary, this trial will evaluate the efficacy of acupuncture for PSVV and explore its central mechanisms. It will provide evidence for acupuncture’s effectiveness in treating PSVV and preliminarily investigate its neuroplasticity effects. Additionally, quality control methods will be implemented to enhance the reliability of results. We anticipate this study will offer guidance for the early treatment of PSVV. Findings will be reported according to the Consolidated Standards of Reporting Trials (STRICTA) guidelines (34).

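### The double-blind label covers all three arms, but participants can be blinded only between acupuncture and sham; the acupuncture versus betahistine comparison is participant-unblinded on a patient-answered primary outcome

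*Protocol article*

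**What the plan says.** The protocol article applies the label three times, each time to the whole trial:

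- Abstract, Methods: "This study is a multicenter, double-blind, randomized controlled trial planned to enroll 234 patients with PSVV from four subcenters".
- Section 2.2: "This is a multicenter, double-blind, randomized, controlled study".
- Discussion: "this study designs a multicenter, randomized, double-blind trial to evaluate acupuncture’s efficacy for PSVV".

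Section 2.6 then describes the blinding itself. On practitioners: "Blinding of the acupuncture practitioners will not be feasible due to the nature of the interventions". Randomization staff open the envelopes and "inform treating physicians of group assignments". The measure meant to keep participants blind, treatment in separate rooms, is described for the acupuncture and sham groups. After the three weeks, "a blinding assessment will be conducted for these two groups", meaning acupuncture and sham.

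Section 2.7 gives the third arm a different form of treatment: "The active drug group will take betahistine mesilate tablets orally three times daily for three consecutive weeks". The two needling arms have sessions and no tablets; the drug arm has tablets, identified by trade name, and no sessions.

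Outcome assessors (section 2.2) and statisticians (section 2.10.1) are stated to be blinded for all groups.

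**The concern.** A three-arm trial with two needling arms and one tablet arm cannot be blinded to participants across all arms unless each arm also receives a dummy of the other form. The article describes no dummy, yet its label makes no distinction between the comparisons.

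This matters because the drug comparison is not incidental. Section 2.1 makes the comparison of acupuncture, sham and active drug a primary objective, the abstract's Discussion presents the trial as the first to compare all three, and section 2.5 includes the drug mean in the sample size. The primary outcome is the DHI. If patients know which treatment they had and rate their own handicap, a difference between acupuncture and betahistine may include an effect of that knowledge on the answers. A reader who relies on the label would not expect this.

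**Working it through.** The point rests on the text and not on a number, so the check sets the statements side by side.

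**Who is blinded, by comparison**

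| Party | Acupuncture vs sham | Acupuncture vs betahistine | Source |
|---|---|---|---|
| Participants | Intended, and checked at end of treatment | Not possible as described | 2.6, 2.7 |
| Acupuncturists | No | No | 2.6 |
| Treating physicians | Told the allocation | Told the allocation | 2.6 |
| Outcome assessors | Yes | Yes | 2.2 |
| Statisticians | Yes | Yes | 2.10.1 |

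The two columns differ in one row, participants. It is also the row that matters most for a patient-answered outcome.

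**Is the drug arm really unblinded to participants?** The article nowhere calls the tablets open. This is inferred from three things in it: section 2.7 sets out each arm's treatment with no placebo tablet and no sham needling of the drug arm; the tablets are named by product; and the blinding check offers real acupuncture, sham acupuncture or undetermined as answers and is not put to the drug arm. All three fit a design with no double-dummy.

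**Does assessor blinding protect the primary outcome?** Section 2.8.1 describes the DHI as a score of disability due to dizziness. It does not say in so many words that the patient completes it, but the Discussion lists self-reported outcomes as a source of possible bias: "Owing to the inability to blind among the acupuncturists, the use of self-reported outcomes". For such an outcome the patient is in effect the assessor. A blinded member of staff who collects the form cannot remove what the patient knows.

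**Do the stated limitations cover it?** That sentence in the Discussion names unblinded acupuncturists, self-report and a possible placebo effect of acupuncture, and accepts that bias may follow. It does not say that the drug arm is unblinded to its participants, and it does not restrict the label to the sham comparison.

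**Is the sample size touched?** No. The inputs in section 2.5 are means 21, 33 and 30, SD 20, α = 0.05 and power 0.90. The grand mean is (21 + 33 + 30)/3 = 28, and the squared deviations sum to 49 + 25 + 4 = 78. With n = 66 per group, the one-way ANOVA noncentrality is 66 × 78/20² = 12.87, which gives power 0.9005. Then 66/0.85 = 77.6, rounded up to 78 per group, and 3 × 78 = 234. The plan's figures reproduce, and none depends on the blinding label.

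**The case against.** Several arguments can be made for the plan.

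- **Assessors and statisticians are blinded in every arm.** This stands, and it limits the point. A reader might infer that the drug comparison is simply open-label. The documents do not support that: it is unblinded to participants and treating staff, with blinded assessors and analysts. Transcranial Doppler and MRI are instrument measures, and the Dizziness and Anxiety Rating Scale includes physician ratings, so the secondary outcomes do not all depend on the patient's own report.
- **Expectation is handled.** It is rated at baseline in each group (section 2.8.2.6). Section 2.10.1 regresses DHI change on expectation, treatment group, baseline DHI, age and sex, with an exploratory interaction of group and expectation. This deserves credit. But a rating at baseline does not capture how knowing the treatment affects answers at weeks 3, 11 and 23.
- **The Discussion already admits bias.** It does, for practitioners, self-report and placebo effect. The drug arm is still not mentioned.
- **Specific effects are already tied to sham.** The Discussion does assign the sham device that role. It stops short of saying that the drug comparison cannot carry the same claim.
- **A journal article is condensed.** True, but the objection is to a claim made three times that section 2.6 does not bear out, and not to a missing detail. A double-dummy would be a core feature of the treatments described in section 2.7.
- **It is only wording.** The correction is indeed wording and changes no arm, endpoint, analysis or sample size. It does change what a result against betahistine can be said to show.

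**Conclusion.** The point holds in a limited form. As written, double-blind is defensible at most for acupuncture versus sham, where participants, assessors and analysts are meant to be blind. It is wrong for acupuncture versus betahistine, where participants and treating staff know the treatment and the primary outcome is the patient's own answer. The contradiction is within the article, between the label and sections 2.6 and 2.7.

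This rests on two readings: that no double-dummy exists, since none is described, and that the DHI is among the self-reported outcomes that the Discussion mentions.

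Three further inferences are tempting and are not made here.

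- **A size of bias.** A reader might express it as a share of the 9-point gap between the assumed means of 30 and 21. The documents give no figure for reporting bias, so any such share would only restate an assumption.
- **Unequal contact.** The needling arms have 3 × 5 = 15 sessions that the drug arm lacks. That is a separate matter from blinding, and relabelling would not address it.
- **Other records.** The documents do not show how the registry entry describes blinding, or how the results will be reported. Nothing is claimed about either.

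**What to change.** 1. In the abstract, section 2.2 and the Discussion, replace the double-blind label with a statement for each comparison: *participant-, assessor- and analyst-blind for acupuncture versus sham; participants and treating staff unblinded, with blinded assessors and analysts, for acupuncture versus betahistine*.
2. State that conclusions on the specific efficacy of acupuncture rest on the sham comparison, and that the comparison with betahistine is interpreted as participant-unblinded on a self-reported primary outcome.
3. Add the unblinded drug arm to the limitations paragraph of the Discussion, beside the unblinded acupuncturists.

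The cost is a few sentences and a weaker, but accurate, claim for the drug comparison. No arm, dummy treatment, endpoint, analysis or sample size has to change.

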**Figure 1 fig1:**
[figure not shown]
Flowchart of the research procedure.

**Table 1 tab1:** Study schedule for data measurements.

Timepoint	Study period				
	Enrolment	Allocation	Treatment	Follow-up	
	Week-1	Week 0	Week 3	Week 11	Week 23
Enrolment					
Eligibility screen	×				
Informed consent	×				
Physical examination	×				
PMH and PTH	×				
CD or CM	×				
Randomization		×			
Interventions					
Group A (*n* = 78)		×	×		
Group B (*n* = 78)		×	×		
Group C (*n* = 78)		×	×		
Assessments					
DHI		×	×	×	×
DARS		×	×	×	×
Vertigo diary		×	×	×	×
SF-36		×	×	×	×
TCD		×	×		
fMRI parameters		×	×		
ERS		×			
Participants safety					
AE		×	×	×	×

*Group A, acupuncture group; Group B, sham acupuncture group; Group C, active drug group; PMH, past medical history; PTH, prior therapy history; CD, concomitant diseases; CM, concomitant medications; Group A, acupuncture group; Group B, sham acupuncture group; Group C, drug control group; DHI, Dizziness Handicap Inventory; DARS, Dizziness and Anxiety Rating Scale; SF-36, 36-Item Short Form Health Survey; TCD, transcranial Doppler ultrasonography; fMRI, functional magnetic resonance imaging; ERS, Expectation Rating Scale; AE, Adverse Event.

